## Abstract

**Background:**

Dementia affects cognitive functioning, physical functioning, activities of daily living (ADLs), and quality of life (QOL). Pharmacological treatments to manage, cure or prevent dementia remain controversial. Therefore development of non-pharmacological approaches to prevent, or at least delay the onset and progression of dementia is urgently needed. Passive exercise is proposed to be such a non-pharmacological alternative. This study primarily aims to investigate the effects of three different forms of passive exercise on QOL and ADLs of institutionalized patients with dementia. The secondary aims are to assess the effects of three different forms of passive exercise on cognitive functioning and physical functioning of institutionalized patients with dementia as well as on care burden of both the primary formal and primary informal caregivers of these patients.

**Methods:**

This is a multicenter randomized controlled trial. Three forms of passive exercise are distinguished; motion simulation (MSim), whole body vibration (WBV), and a combination of both MSim + WBV. Intervention effects are compared to a control group receiving regular care. Institutionalized patients with dementia follow a six-week intervention program consisting of four 4–12 min sessions a week.

The primary outcome measures QOL and ADLs and secondary outcome measure care burden are assessed with questionnaires filled in by the primary formal and informal caregivers of the patient. The other secondary outcome measures cognitive and physical functioning are assessed by individual testing. The four groups are compared at baseline, after 6 weeks of intervention, and 2 weeks after the intervention has ended.

**Discussion:**

This study will provide insight in the effects of different forms of passive exercise on QOL, ADLs, cognitive and physical functioning and care burden of institutionalized patients with dementia and their primary formal and informal caregivers. The results of this study might support the idea that passive exercise can be an efficient alternative for physical activity for patients not able to be or stay involved in active physical exercise.

**Trial registration:**

The Netherlands National Trial Register (NTR6290). Retrospectively registered 29 March 2017.

## Background

Dementia is a life changing condition that is characterized by progressive cognitive decline and motor deficits, often leading to psychological symptoms, decline in quality of life (QOL) and the ability to perform activities of daily living (ADLs). These disabilities lead to loss of autonomy and need for (in)formal care, in most cases even institutionalization is required. Institutionalization, however, often results in a further decline in QOL of the patient [1].

To date no cure for dementia is developed. Pharmacological treatments have been unsuccessful and often have many side effects. Therefore, over the past few years there has been a growing interest in non-pharmacological interventions to limit the adverse effects of dementia. Physical exercise is one example of such a non-pharmacological intervention. In multiple studies positive effects of physical exercise on QOL, ADLs, physical and cognitive functioning of patients with dementia were found [2–7]. Physical exercise thus seems to be an effective treatment strategy to limit the adverse effects of dementia. However, due to physical decline, behavioral problems and limited time of caregivers to accompany patients, engaging in physical exercise is not possible for most institutionalized dementia patients.

It is proposed that passive exercise can be an efficient alternative for physical exercise to enhance QOL and ADLs in institutionalized patients with dementia. Three forms of passive exercise that can be employed with a robotized movement platform (Fig. 1a, b) are distinguished; motion simulation (MSim), whole body vibration (WBV), and a combination of both MSim + WBV.

**Fig. 1 Fig1:**
[figure not shown]
Motion simulation devices **a** The balancer with a chair, screen and control panel, and **b** the wheelchair pod with a wheelchair platform and television screen (identical control panel as in Fig. 1a is not depicted). Both platforms are used to provide the MSim, WBV and MSim + WBV intervention sessions

During MSim movies of multiple activities from various perspectives are shown on a television screen. During these movies the robotized platform moves synchronically with the activities on the screen. Also matching sounds and music are played. Altogether MSim stimulates the visual, auditory, tactile, and proprioceptive system of a participant. To the best of our knowledge, to date MSim in this specific form has not yet been studied. However, other studies that employed either visual or auditory stimulation showed that video and music interventions can improve alertness and happiness, promote social behavior, and reduce behavioral disturbances as well agitated behavior of patients with dementia [8–10].

During WBV, participants are exposed to mild vibrations via contact with a vibration source. Thereby, WBV provides tactile and proprioceptive input to the participant. The intensity of WBV can be controlled by adjusting the frequency, the amplitude (peak to peak displacement), and the time of exposure. Multiple studies reported that mild vibrations (30–40 Hz) can improve physical performance and health related components such as increased muscle strength, mobility, balance and lower blood pressure [11–14]. Furthermore WBV was also found to improve cognitive functioning, for example attention and inhibition of schoolchildren, young adults and persons with attention deficit hyperactive disorder [15, 16].

The exact working mechanisms of WBV and MSim remain unknown. However, we assume that the following mechanisms may play a role. WBV can induce brain activation, especially in the sensory (motor) cortex. Skin mechanoreceptors, e.g. Meissner corpuscles, are sensitive for 30 Hz stimulation and activation of these receptors leads to activation of the spinothalamic pathway and the medial lemniscal pathway, both ending in the sensory motor cortex [17–19]. The visual, auditory and sensory stimuli of MSim on the other hand can elicit brain activation in the different layers of the visual cortex, the cochlear nucleus in the brainstem and to a lesser extent than WBV in the sensory motor cortex [18]. Moreover, it is thought that the large translational and rotational movements of MSim will also increase signaling of the vestibular system to for example the cerebellum, thalamus and reticular formation in order to maintain an upright posture [20]. Activation of the above mentioned areas and pathways may induce increased blood flow in and synaptic strengthening of these specific areas and pathways. Furthermore neurite outgrowth and functioning of underlying neurotransmitter systems can be enhanced [21–25]. For both MSim and WBV association areas will receive input from the activated sensory areas, causing a diffuse activation of brain regions [26]. We believe that during MSim a more diverse sensory integration of the different stimuli will take place, while during WBV primarily the sensory (motor) cortex processing vibration stimuli will be activated. When combining MSim and WBV it is thought that the combination of high activation in the sensory (motor) cortex (WBV) and sensory integration of the visual, auditory and sensory stimuli (MSim) will enhance the effects seen for WBV and MSim alone.

Although MSim is already being used in multiple health care settings, any effects of MSim alone or combined with WBV have not yet been established. The current study primarily aims to investigate the effects of the three different forms of passive exercise on QOL and ADLs of institutionalized patients with dementia. The secondary aims are to assess the effects of the three different forms of passive exercise on cognitive functioning and physical functioning of institutionalized patients with dementia as well as on care burden of both the primary formal and primary informal caregivers of these patients. Cost-effectiveness of the interventions will also be analyzed. It is hypothesized that MSim and WBV, due to their own specific working mechanisms, both will lead to an improvement in QOL, ADLs and cognitive functioning, but that the combination of MSim and WBV will lead to a stronger cognitive effect as a results of complementary working mechanisms. In addition, it is hypothesized that improvement in ADLs and improved cognition will lead to more independent and better daily functioning of the patient, causing a reduction in need for care and consequently lower the care burden of the primary formal and informal caregiver..

## Methods

### Study design and setting

This is a single blind randomized controlled trial. The study will be conducted in the closed wards of nursing homes in the north of the Netherlands. The effects of three different types of passive exercise will be studied and compared to a control group receiving regular care.

The protocol follows the Standard Protocol Items: Recommendations for Interventions Trials (SPIRIT) 2013 statement [27]. The study protocol is approved by the medical ethics committee of the University Medical Center Groningen (the Netherlands), according to the principles of the Declaration of Helsinki, and is registered with The Netherlands National Trial Register (NTR6290, http://www.trialregister.nl).

### Participants and eligibility criteria

Institutionalized older adults with dementia will be included in this multicenter, single blind randomized controlled trial. People are eligible if they are officially diagnosed with some form of dementia, aged 65 years or older, not physically active for more than 10 min a day. Participants will be excluded if they have a contra-indication for exercise, have a serious auditory disorder, are color blind, and/or excessively use alcohol or drugs.

### Study procedures

The participants of this study will be recruited via the medical staff of nursing homes. The medical staff and nurses, who are informed about the aim and procedure of the study, select potential participants within the different wards of the nursing homes. The potential participants and their legal representatives then receive an information letter with informed consent. The legal representatives of the potential participants can provide written informed consent, and in addition patients will have to orally agree to participate. After informed consent is given by the legal representatives, participants will be screened for eligibility.

Measurements for cognitive and physical function are administrated by trained research assistants who are blinded for group allocation. Questionnaires for QOL, ADLs and care burden are given or send to respectively the primary formal and primary informal caregiver. Tests and questionnaires for all outcome measures are assessed at baseline (T0), after the intervention period of six weeks (T1) and two weeks after the intervention has ended (T2). All test moments of a given participant are performed at the same time of the day and are assessed by the same research assistant. Also the questionnaires for both the primary formal and primary informal caregiver are filled in by the same person on each given time point. An overview of the enrollment and study design is given in Fig. 2.

**Fig. 2 Fig2:**
[figure not shown]
Flowchart of the study processes

#### Randomization

After baseline measurements and stratification for gender, MMSE score, age and nursing home, participants are randomly assigned (1:1:1:1 allocation ratio) to one of the four groups (MSim, WBV, MSim + WBV or regular care which serves as the control condition) by using random numbers. The randomization procedure is performed by a blinded scientist who is not related to the study.

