#### Cognitive functioning

To evaluate the effects of passive exercise on cognitive functioning a neuropsychological test battery that covers de subdomains global cognitive functioning, executive functioning and verbal memory is used.

Global cognitive functioning is measured using the Mini Mental State Examination (MMSE) [38].The MMSE is a brief 20 item questionnaire test that is used to screen for cognitive impairment. The items refer to orientation, attention, memory, recall, and processing verbal and written information. Scores on this test can range from 0 to 30, a higher score reflects a higher level of global cognitive function.

To measure attention the Deary-Liewald simple reaction time task (SRT) [39] is used. During the SRT participants have to press a key, as quickly as possible in response to a single stimulus. The stimulus consists of a black cross appearing in a white square. Five practice trials are given (the practice trial can be repeated up to a maximum of 3 times to make sure the participant fully understands the task), after which instructions are repeated. The official test consists of a minimum of 15 trials. The test stops if the participant has 15 correct responses, correct being a response within the time limits of 150–3000 ms. Means and standard deviations are measured for each participant. Also the number of correct and incorrect (premature and anticipated) responses is measured.

The Stroop test is used to measure attention and inhibition [40]. It consists of three subtasks, all performed as quickly and accurately as possible within 45 s. For the first subtask a card is used with names of 4 colors (‘blue’, ‘green’, ‘red’, ‘yellow’) printed on it in black ink. Participants have to name the right words in the right sequence (left-right, top-bottom), as fast as possible. For the second subtask a card with colored blocks (blue, green, red, and yellow) is used. Participants have to name the right color of the block in the right sequence, as fast as possible. During the third subtask a card with names of colors (‘blue’, ‘green’, ‘red’, ‘yellow’) printed in opposite colors (e.g. ‘red’ written in blue ink or ‘yellow’ written in green ink) is presented to the participant. The participant now has to name the ink of as many words as possible in the right sequence. The score for each subtask consists of the number and the accuracy (%) of correctly named words or colors, a higher number and percentage reflects better inhibition.

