### Statistics

For each group, descriptive statistics of the sample’s sociodemographic and clinical characteristics at baseline will be determined. Analyses of covariance (continuous, normally distributed data) or non-parametric alternatives (ordinal, non-normally distributed data) will be used to examine differences between groups at baseline.

Since all primary outcome measures and some of the secondary outcome measures result from questionnaires, they will be of ordinal level of measurement and probably have a skewed distribution. Therefore, non-parametric tests will be used to analyze the data from the questionnaires. Gain scores (post-test minus pretest and follow-up test minus pretest/posttest) will be calculated and the differences between the groups will be analyzed using Kruskall-Wallis tests followed by Bonferoni corrected Mann-Whitney tests for paired comparisons.

The outcome measures related to cognitive and physical function will be of continuous level. If the data satisfy the assumptions, analyses of covariance will be used with scores on cognitive tests at T1/T2 as dependent variables, pretest scores as covariates and group (experimental groups, control group) as between-subjects factor. If the data do not meet the assumptions repeated measures analyses of variance or non-parametric methods with gain scores will be considered. Post-hoc tests will be performed with Bonferoni corrections for multiple comparisons. The data will be analyzed both according to intention-to-treat method (irrespective of adherence to intervention) as per-protocol (for selection of participants with sufficient adherence).

Missing data of items within questionnaires are substituted as prescribed for the individual questionnaires. If no prescription is available, the maximum likelihood method is used to substitute the missing values. Based on the internal consistency of the questionnaires, the maximum number of substituted values will be determined (Cronbach’s alpha >.80, max 50% of the items can be substituted).

A *p*-value of < 0.05 will be used to assess statistical significance. For all tests power and effect size calculations will be performed. Effect sizes will be calculated with Cohen’s d to measure the magnitude of difference of gain score measurements between each experimental and control group. Values benchmarking small, medium and large effect sizes: d = .20, d = .50, d = .80 [48].

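### The planned tests leave out the factors used to stratify randomisation, so they lose power to the extent that gender, MMSE score, age or nursing home predict change

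*Protocol article*

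**What the plan says.** **Allocation.** Under Randomization, the protocol article states: "After baseline measurements and stratification for gender, MMSE score, age and nursing home, participants are randomly assigned". Allocation is 1:1:1:1 to three intervention arms and regular care. The only mechanism given is "by using random numbers"; blocks, minimisation and cut-points for age and MMSE are not described.

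**Analysis.** Under Statistics, every primary outcome is treated as ordinal questionnaire data. Gain scores are formed, and "the differences between the groups will be analyzed using Kruskall-Wallis tests followed by Bonferoni corrected Mann-Whitney tests". Cognitive and physical outcomes get ANCOVA with "pretest scores as covariates and group (experimental groups, control group) as between-subjects factor". If assumptions fail, repeated measures ANOVA or rank methods on gain scores are the fallback, again with no mention of the stratification factors.

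**Raters.** Under Study procedures, the tests of a given participant "are assessed by the same research assistant" at all time points. Each caregiver questionnaire is likewise completed by one and the same person throughout.

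**The concern.** Stratification helps in two ways: it protects against chance imbalance, and it makes the arm difference less variable when the factors predict the outcome. The second benefit reaches the test only if the analysis uses the factors. If it does not, the variance they explain stays in the error term. The test then judges a more precise difference against a yardstick that is too wide.

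The primary outcomes are most exposed. Kruskal-Wallis and Mann-Whitney tests in their ordinary form have no place for a stratum or a covariate, so a later analysis plan could bring the factors in only by changing the tests. The sample size was derived from the Stroop test, a secondary outcome, so the article does not establish power for the primary outcomes. Any avoidable loss there raises the chance of missing a real effect.

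**Working it through.** **Inputs from the article.** Four stratification factors; four arms; 49 per arm including 15% dropout, so about 42 evaluable (49 × 0.85 = 41.7); the tests as stated above.

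**The figure of 49.** It serves here only to turn percentages into participants. The article gives neither the number of measurements nor their correlation, so its inputs do not determine 49. The figure is attainable: the between-group effect with 2 measurements and correlation 0.4 needs 41, and 41/0.85 = 48.2, rounded up to 49. It is not in dispute here.

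**Assumed input.** R2, the share of variance in the analysed score (gain score, or score after pretest adjustment) that the stratification factors explain. The article gives no value, so a range is shown.

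**Which factors enter which test.**
- Questionnaires (all primary outcomes): none.
- ANCOVA for MMSE: baseline MMSE, as its pretest score.
- ANCOVA for every other cognitive or physical test: none.

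**Analytic check, assuming effective balance.** The true variance of the arm difference is (1 − R2) times the variance the unadjusted test assumes. Hence:
- SE ratio = 1/√(1 − R2)
- true size of a nominal 5% test = 2[1 − Φ(1.96/√(1 − R2))]
- share of sample lost at 80% power = 1 − [2.80/(1.96/√(1 − R2) + 0.84)]²

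| R2 | SE ratio | True size | Sample lost | Of 49 per arm |
|---|---|---|---|---|
| 0 | 1.00 | 5.0% | 0% | 0 |
| 0.05 | 1.03 | 4.4% | 3.5% | 1.7 |
| 0.10 | 1.05 | 3.9% | 7.2% | 3.5 |
| 0.20 | 1.12 | 2.8% | 14.7% | 7.2 |

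Worked line for R2 = 0.10: 1.96/√0.90 = 2.066; 2.80/(2.066 + 0.84) = 0.9635; 1 − 0.9635² = 0.072; 0.072 × 49 = 3.5.

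**Simulation check.** 4,000 runs per setting. Assumed: 7 homes of 24 participants (42 per arm), permuted blocks of four within home, home as the only predictive factor, and a two-arm effect of d = 0.6 for power.

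| Home share of gain-score variance | Kruskal-Wallis size | t-test size, unadjusted | Power, t-test unadjusted | Power, home in model |
|---|---|---|---|---|
| 0 | 0.048 | 0.050 | 0.78 | 0.78 |
| 0.05 | 0.044 | 0.047 | 0.77 | 0.79 |
| 0.10 | 0.034 | 0.040 | 0.78 | 0.81 |
| 0.20 | 0.030 | 0.033 | 0.82 | 0.86 |
| 0.30 | 0.020 | 0.026 | 0.82 | 0.90 |

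With home in the model, size stays at 0.048 to 0.053.

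**If allocation does not balance homes** (share 0.20): the unadjusted SE is correct (ratio 1.00) and t-test size is 0.055, within simulation error of 5%. Precision is still lost: the average SE is 0.214 unadjusted and 0.202 with home in the model.

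**The case against.** **Home and rater differences.** A reader might infer that differences between homes or raters are ignored and could distort the comparison. The article does not support this. A stable strict or lenient rating habit cancels in a gain score, or is taken up by pretest adjustment, when the same person rates throughout. Only differences between homes in change over the follow-up remain. Participants are randomised individually, so these cost precision and do not bias the comparison. This objection stands.

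**Standard errors too wide.** This is tempting as a flat statement, but it needs factors that predict change and allocation that truly balances them. Assuming two levels each for gender, age and MMSE, and seven homes, there are 2 × 2 × 2 × 7 = 56 strata for 196 participants, or 3.5 per stratum across four arms. With no mechanism described beyond random numbers, balance is uncertain. For the primary rank tests the effect is in any case on test size and power, not on a reported standard error. This also stands.

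**Size of the loss.** Taking R2 × 49 gives 5 to 10 participants per arm for R2 of 0.10 to 0.20. That overstates the loss under effective balance, because stratification has already reduced the true variance and only the critical value is too strict.

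**Condensed article.** One may say that further covariates belong in the analysis plan. For the ANCOVAs this has some force, since the listed terms may not be exhaustive. It has little for the primary outcomes, where the named tests themselves exclude the factors.

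**Conclusion.** The point holds as a matter of efficiency. The primary analyses, as fixed in the article, use none of the four stratification factors. The ANCOVAs as described use only baseline MMSE, and only for the MMSE outcome. Power is lost to the extent that the factors predict change. With effective balance the tests are also conservative: true size is about 4.4% to 2.8% for R2 of 0.05 to 0.20, and the loss at 80% power is about 7% to 15% of the sample for R2 of 0.10 to 0.20 (about 3.5 to 7 of 49 per arm). At R2 = 0 nothing is lost. These R2 values are assumptions; nothing in the article says how far the factors predict change.

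The omission does not bias the comparison, and it does not inflate type I error where stratification balances the factors. It would therefore not undermine a positive result. It makes a real effect somewhat easier to miss. The change is worth making because it costs almost nothing even when the factors turn out not to matter (power 0.78 either way at a home share of 0).

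**What to change.** - **Questionnaires, if rank tests are kept:** stratify by nursing home, with a stratified Kruskal-Wallis test overall and van Elteren tests for the pairwise comparisons. This uses home only; crossing it with the other factors would make the strata too small.
- **Questionnaires, otherwise:** replace the rank tests with a baseline-adjusted model (proportional odds or ANCOVA) containing nursing home, gender, age and baseline MMSE.
- **Cognitive and physical ANCOVAs:** add the same factors to group and pretest score. Where MMSE is the outcome, enter baseline MMSE once.

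All four factors are known before allocation. Naming them before the data are seen also rules out later choice of covariates.

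**Cost:** a few degrees of freedom. The model option is a real change of primary method, not an added term. The number of homes is not given; very small homes may need pooling or a random intercept.
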